### Randomisation, allocation concealment and blinding

The unit of randomisation (cluster) is the general practice, and these have been randomised using a minimisation approach that maximises the balance across two baseline variables. These baseline variables are annual chlamydia testing rates among 16- to 29-year-old men and women for the 12-month period prior to commencing ACCEPt-able and size of the practice (number of patients seen each year). Practices have been progressively randomised into ACCEPt-able once their participation in ACCEPt is complete. The trial statistician is located at a site away from any of the participating general practices. The statistician allocated each general practice according to the computer-generated algorithm and informed research staff of the randomisation outcome for each practice. Blinding of general practices and GPs to their trial allocation is not possible given the nature of the intervention.

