### Data collection

We have installed GRHANITE™ [24], a data extraction tool developed by the University of Melbourne, at all general practices participating in ACCEPt-able. The tool extracts anonymous data about all consultations including age and gender of the patient, a unique non-identifying patient code that enables us to track repeat visits to any participating general practice, chlamydia pathology test ordering, and test results. GRHANITE™ encrypts data on the general practice computer and electronically exports them to a secure database at the University of Melbourne once per week. These data are used to calculate chlamydia testing rates for participating GPs. In addition, we collect data for factors that might confound associations with our outcome of chlamydia testing rates. These data include the individual’s age and gender and GP’s years of experience in general practice, as well as area level data such as the size of the underlying population and the socioeconomic profile of the area according to the Australian Bureau of Statistics Index of Relative Disadvantage.

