### Sample size

The intra-cluster correlation for chlamydia testing in participating general practices in the 12 months prior to commencing ACCEPt-able was 0.02. The cluster size of an average of 700 patients aged 16 to 29 years seen in each participating general practice per year gives a design effect of 15. With 60 general practices available for randomisation and an average of 700 patients per practice, we get an effective sample size of 2800 (calculated by dividing total patients by design effect = 60 × 700 = 42,000; 42,000/15 = 2800). A sample size of 2800 patients across all four study groups will allow us to detect a 5 % decrease in testing from 20 to 15 % between any two groups with 94 % power. A total of 15 general practices will be randomly allocated to each of the four study arms.

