### Statistical analysis

Analyses will be according to intention to treat. The effect of removal of incentives and removal of feedback on chlamydia testing rates will be investigated by comparing the study groups as shown in the table below (Table 1). We will also investigate the effect of each of the two interventions on chlamydia testing rates as main effects exploiting the factorial nature of the design. Thus, the effect of removing financial incentives will be assessed by comparing randomised groups 2 and 3 with groups 1 and 4. Similarly, the effect of removing audit plus feedback will be assessed by comparing groups 1 and 3 with groups 2 and 4. The advantage of a factorial design is that it includes all patients in assessing the effectiveness of the two separate interventions, maximising the power of the study. However, this is based on the assumption that the effect of the two interventions is at least additive, and that there is no negative interaction between them, which will be tested. Formal statistical comparisons will be based on generalised mixed models that can account for cluster (general practice), GP and patient variability. Generalised estimating equation (GEE) approaches, with robust standard errors, will be adopted using STATA software. Hierarchical logistic regression models will be used to examine the impact of each of the two interventions over time on the proportion of patients who have a chlamydia test during the follow-up. Analyses will be adjusted for the chlamydia testing rate at each general practice immediately prior to commencing ACCEPt-able.

**Table 1 Tab1:** Comparison of groups for analysis

Comparison	Removal of audit and feedback—continue financial incentives only	Removal of financial incentives—continue audit plus feedback only	Removal of financial incentives and audit plus feedback	Continue financial incentives and audit plus feedback
	Group 1	Group 2	Group 3	Group 4
Removal of financial incentives versus other	Groups 2 and 3 versus groups 1 and 4			
Removal of audit and feedback versus other	Groups 1 and 3 versus groups 2 and 4			

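### The stated adjustment names the prior testing rate but not practice size, the other minimisation variable; if size predicts testing, the tests will be somewhat conservative

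*Protocol article*

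**What the plan says.** The section on randomisation, allocation concealment and blinding says that practices were "randomised using a minimisation approach that maximises the balance across two baseline variables". It then names the two. The first: "These baseline variables are annual chlamydia testing rates among 16- to 29-year-old men and women for the 12-month period prior to commencing ACCEPt-able". The second is "size of the practice (number of patients seen each year").

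The Statistical analysis section gives one sentence on covariates: "Analyses will be adjusted for the chlamydia testing rate at each general practice immediately prior to commencing ACCEPt-able". Practice size does not appear in that section. On standard errors it says: "Generalised estimating equation (GEE) approaches, with robust standard errors, will be adopted using STATA software". Generalised mixed models and hierarchical logistic models are named beside this.

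The Data collection section lists further variables that might confound the outcome. The nearest to practice size is "area level data such as the size of the underlying population", which describes the area, not the practice. That section does not commit the analysis to adjusting for any of them.

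**The concern.** Minimisation makes the arms more alike on practice size than chance would. If size is related to the testing rate, that variation has been largely removed from the contrast between arms. A model without size still leaves it in the residual between-practice variance, so the standard error allows for chance imbalance that the allocation prevented. Robust GEE standard errors account for correlation within practices; they do not credit balance created by the allocation.

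At stake are confidence intervals wider than they need be, a test run below its nominal level, and some lost precision in a trial of 59 clusters. A covariate that is already known would go unused. The choice of size as a minimisation factor suggests that the investigators thought it might matter.

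**Working it through.** **The plan's own figure.** Inputs from the Sample size section: ICC 0.02, 60 practices, 700 patients each, 20 % against 15 %. Two-sided alpha of 0.05 is assumed, as it is not stated.

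- Design effect: 1 + (700 − 1) × 0.02 = 14.98, about 15. Effective size: 60 × 700 / 15 = 2800.
- Power = Φ[(0.05 − 1.96 × √(2 × 0.175 × 0.825 / n)) / √((0.2 × 0.8 + 0.15 × 0.85) / n)].
- n = 1400 per side (two arms pooled against two) gives 93.6 %, against 94 % stated.
- With 59 practices, 59 × 700 / 15 / 2 = 1377 per side gives 93.3 %, against 93 % stated in the Discussion.

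This calculation uses the raw ICC and gives no credit for the planned adjustment for baseline rate.

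**Effect on standard error and type I error.** 59 practices were minimised into four arms on two three-level factors, with the best-balancing arm favoured with probability 0.9 (the protocol does not give the algorithm's settings, so these are assumptions). Practice-level outcomes were analysed by a linear model with both factorial effects and the baseline rate, with and without size, in 3000 runs per setting. R² is the share of residual practice-level variance, after baseline rate, explained by size. It is assumed, not taken from the protocol.

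| R² | Mean SE, size omitted | Empirical SD | SE ratio | Type I error, size omitted | Type I error, size included |
|---|---|---|---|---|---|
| 0 | 0.260 | 0.265 | 0.98 | 5.0 % | 5.0 % |
| 0.05 | 0.260 | 0.252 | 1.03 | 3.7 % | 4.2 % |
| 0.10 | 0.260 | 0.255 | 1.02 | 4.3 % | 5.4 % |
| 0.20 | 0.260 | 0.240 | 1.08 | 3.5 % | 5.3 % |
| 0.30 | 0.261 | 0.228 | 1.14 | 2.8 % | 5.1 % |

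The Monte Carlo standard error of a 5 % rate is √(0.05 × 0.95 / 3000) = 0.4 percentage points, so the rows at 0.05 and 0.10 differ only by noise. The trend at 0.20 and 0.30 is clear.

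**Effect on main-effect power.** Let b be the share of between-practice variance explained by the baseline rate (assumed). In this step R² applies to the between-practice component only. The variance of a practice mean, in units of p(1 − p), is

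v = 0.02 × (1 − b) × (1 − R²) + 0.98 / 700,

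and the effective n per side is 29.5 / v. For b = 0.25 and R² = 0, v = 0.0150 + 0.0014 = 0.0164 and n = 1799.

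| b | R² = 0 | R² = 0.09 | R² = 0.25 | R² = 0.30 |
|---|---|---|---|---|
| 0 | 93.3 % | 95.1 % | 97.7 % | 98.3 % |
| 0.25 | 97.7 % | 98.5 % | 99.4 % | 99.6 % |
| 0.50 | 99.7 % | 99.9 % | above 99.9 % | above 99.9 % |

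Once the baseline rate is credited (b = 0.25 to 0.50), adding size gains about 0.1 to 2 points over R² = 0.09 to 0.30, and nothing at R² = 0.

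**The case against.** **The covariate list may not be closed.** The sentence does not say that the prior rate is the only covariate, the article mentions other possible confounders, and an analysis plan that is not shown could add size. This stands in part: a reader might infer that size is excluded from the analysis, and the text does not say so. But the article does more than leave covariates to another document. It names a covariate, and names one of the two variables that governed allocation. The public statement should match the design.

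**The harm is conditional.** The prior testing rate is the same outcome measured a year earlier and is likely to be the strongest practice-level predictor. Size may add little or nothing, and then nothing is lost. This stands in full. A reader might infer that precision is certainly lost; the protocol gives no figure that would show it.

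**The size of the effect is easily overstated.** It is tempting to start from the stated 93 % and conclude that adding size would lift power to about 95 % or 98 %. That holds only if the baseline rate explains nothing, although it is already in the planned model. Likewise, the simple inflation factor 1/√(1 − R²) assumes perfect balance on size. At R² = 0.20 it gives a standard error 12 % too wide and alpha of 2.8 %, where the simulation gave 8 % and 3.5 %. At R² = 0.30 it gives 20 % and 1.9 %, against 14 % and 2.8 %. Both objections stand, and the smaller figures are the ones to use.

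**Conclusion.** The mismatch is on the page: two minimisation variables, one named covariate. Its direction is also clear: any error is conservative. A reader might take an unadjusted balancing factor to mean a biased estimate or excess false positives; neither follows, and no simulated type I error with size omitted exceeded 5.0 %.

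The size depends on an unknown. Over an assumed R² of 0 to 0.30, standard errors run from not inflated to about 14 % too large, type I error falls from 5.0 % to about 2.8 %, and the main-effect power forgone is probably about 0.1 to 2 points. The planned interaction test has less power than the main effects and so has more room to benefit.

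These figures rest on a linear practice-level model and assumed minimisation settings, not on a replica of the planned logistic GEE. The point is minor: a free improvement, not a threat to the trial's conclusions.

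**What to change.** Amend the covariate sentence in the Statistical analysis section to say that analyses will be adjusted for both minimisation variables: the practice's testing rate over the 12 months before ACCEPt-able, and practice size as used in the minimisation (for example, the log of the number of patients seen per year). If an analysis plan already includes size, the two documents need only be aligned.

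The cost is one practice-level degree of freedom among 59 clusters and a change of wording. No new data are needed, because minimisation required the size of every practice at allocation. With a logistic link, the odds ratio becomes conditional on size as well as on the baseline rate, which should be noted when results are reported. The change should be made before outcome data are examined, so that it is not a post hoc choice.

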### Interviews with GPs and general practice staff

To evaluate the views and acceptability of incentive payments and external audit plus feedback, we will conduct semi-structured qualitative interviews with a sample of about 28 GPs (7 from each study arm) and 20 other staff including nurses and practice managers (5 from each study arm) towards the end of the ACCEPt-able intervention period. Recruitment numbers will be dependent upon reaching saturation of themes arising from iterative data analysis. All interviews will be conducted by telephone. Participants will be reimbursed for each interview ($AU 100 for GPs; $AU 40 for practice nurses/managers). The use of different sources of information (GPs, nurses, practice managers) is consistent with best practice in qualitative research (i.e. “triangulation” methods). The interview will cover (i) views and acceptability of audit plus feedback and incentive payments and their removal; (ii) perceived facilitators and barriers to preventive care activities; (iii) impacts of the trial on the general practice; and (iv) any contextual factors that may impact on the general practice’s workload and patient mix. Interviews will be tape-recorded and transcribed verbatim. After multiple readings of the text, data will be coded utilising a qualitative data software package. Consensus on main themes and sub-themes will be reached by multiple coders assigned to each transcription. Analyses will explore the acceptability of financial incentives and audit plus feedback and identify any barriers and facilitators to chlamydia testing in general practice.

### Cost-consequence evaluation

A cost-consequence analysis comparing costs and consequences in the scenarios for continuation/discontinuation of financial incentives and audit plus feedback activities will be undertaken. Costs (including incentives, travel, time) and consequences in the following scenarios will be compared: (i) financial incentives continue but audit plus feedback activities are removed; (ii) financial incentives are removed but audit plus feedback activities continue; (iii) both financial incentives and audit plus feedback activities are removed; and (iv) financial incentives and audit plus feedback activities continue. The consequence to be considered in each scenario is the proportion of people tested in the target population.

### Trial status

The trial has been registered on the Australian and New Zealand Clinical Trials Registry (ACTRN12614000595617). A total of 59 general practices have been recruited to ACCEPt-able with only one eligible practice refusing to participate (98 % response rate). The intervention period will be complete on 2017 with trial results due late 2017.

## Discussion

This will be the first RCT to examine the impact of removal of financial incentive payments and audit and feedback on the chlamydia testing behaviour of GPs. As both the Australian and UK governments act to reduce payments or raise the threshold to be eligible for payments, we urgently need robust epidemiological data assessing the potential impact this might have on provider performance and patient outcomes. Further, audit plus feedback are key components of managing quality improvement in general practice in Australia and the UK [4, 5], and while research suggests that it can be effective in modifying provider behaviour [6], there is no RCT evidence available about the impact its removal may have on GP activity.

The interactions between intrinsic motivation of doctors and extrinsic rewards such as financial remuneration are complex. It is difficult to judge the point at which incentivized behaviours become normalised within standard practice, rendering financial incentives superfluous. A recently published study examined the impact of removing financial incentives on provider behaviour in the Kaiser Permanente health plan in the USA. This observational study found that when financial incentives were removed from two indicators, there was a small decrease of about 3 % per year for screening for diabetic retinopathy and 1.6 % per year for cervical cancer screening [13]. A more recent analysis of observational data examined the effect of withdrawing incentives for eight clinical quality indicators from the QOF in the UK including influenza immunisation, lithium treatment and blood pressure, cholesterol and blood glucose monitoring. This study found that mean levels of performance were generally stable, in both the short and long term; however, there was a small but statistically significant drop in influenza immunisations [25].

This trial has several strengths. Firstly, a factorial RCT design is the most powerful and efficient method to investigate the impact of removing financial incentives and audit plus feedback on GP behaviour. In addition to the effects of each treatment, factorial design provides some data on the interaction that may exist between two interventions. Hence, we will have evidence about whether the effect of the removal of incentives varies according to whether or not practices receive audit plus feedback as well. Secondly, the inclusion of qualitative interviews will collect valuable data about the perceived importance of incentive payments and audit and feedback to general practice staff. These qualitative data will be assessed alongside the trial results, providing greater insight to the RCT results. Finally, the cost-consequence analysis also strengthens this trial. This trial will gather evidence to inform future policy on primary care reform, and as part of this, the cost of the interventions investigated and the outcomes associated with each intervention are of paramount importance to decision makers. A cost-consequence analysis involves itemising the different intervention components and their costs and the outcomes (chlamydia testing rate) for each trial group. We have selected this form of analysis because, unlike a cost-effectiveness analysis, the cost-consequence approach clearly lists the costs and outcomes associated with each intervention enabling decision makers to see the actual data. Unfortunately, one clinic refused to participate in the trial. However, this has negligible impact on our statistical power as we will still have 93 % power to detect a drop in chlamydia testing rates from 20 to 15 % between any two groups.

### Conclusion

While annual chlamydia screening is a key preventive health activity for young adults in Australia and the UK [18, 20], the results of this trial will have preventive health implications well beyond the content area of chlamydia. Incentive payments and audit plus feedback are already used for several preventive health activities in primary care in Australia and the UK including asthma management, cervical cancer screening and cardiovascular risk assessment. Our results will be readily transferable to these other preventive health activities. This trial is particularly timely as we will increase the understanding of the impact of financial incentives and audit and feedback on primary care provider behaviour when governments are looking for opportunities to control healthcare budgets and maximise clinical outcomes for money spent.

## Abbreviations

ACCEPt: Australia Chlamydia Control Effectiveness Pilot
GP: General practitioner
P4P: Pay for performance
QOF: Quality and outcomes framework
